Accelerometers were pre-tested with eleven 2–9-year-old children. The children engaged in free movement, play, and games on a test track field for one hour for determination of how scurrying-type movements appear in the readings. Another test, on a running track, tested speeds ranging from slow walking to participants’ maximum rate of running. In addition, accelerometers were piloted in free-living conditions with 10 children aged 4–7 for one week. In these tests, the acceleration signal behaved as expected, in other words, the MAD-value was higher for younger (smaller) children at the same speed and different activity intensities could be identified from the data.

### The movement-to-music DVD’s production and pre-testing

In spring 2014, three distinct movement-to-music video programs were prepared, by the Sibelius-Academy music-education students in course specifically on children’s music programs. The music was composed and arranged with lyrics. Further video programs were produced for the study specifically as part of a training course on children’s music and videos. Two of the videos last about 10 min each, including two songs and their movement instructions. There are three songs in all, because the title song, “Mutaveijarit” (or “The Mud Mates”) is part of both tracks (see Table 2). The third video includes all songs, with movements but without any verbal instructions, and it lasts about 12 min.

**Table 2 Tab2:** Details of the music used for the movement-to-music DVD

Name of song	Music, lyrics, and arrangement	Music genre	Tempo (bpm^a^)	Motivational quality of the video vs. music group (BMRI-2^b^)
Video 1: Mutaveijarit ja karibialainen kala (10 minutes)				
”Mutaveijarit”	[name] and Mutaveijarit	Children’s rock	94	34.6 vs. 33.7
“Karibialainen kala”	[name]	Children’s Latin	128	34.0 vs. 31.9
Video 2: Kuraa ja mutaa (10 minutes)				
”Kuravelli”	[name] and Mutaveijarit	Children’s folk	124	32.5 vs. 31.4
“Mutaveijarit”	[name] and Mutaveijarit	Children’s rock	94	
Video 3: Mutaveijarit kooste (12 minutes)				
”Mutaveijarit”,”Karibialainen kala”,”Kuravelli”, and again”Mutaveijarit”				

^a^Beats per minute

^b^Brunel Music Rating Inventory-2 (max. 42 points)

To rate the motivational qualities of the three songs, a panel of eight physiotherapists (all female and comparable to the adult intervention participants in age, race, and cultural background) assessed each song by using the BMRI-2 [28, 29]. Another reason for pre-testing was to find out the influence of visual stimuli on the responses to the music. The BMRI-2 was translated into Finnish by investigators involved in the present study.

Each song was rated with a one number from 1 (“Strongly disagree”) and 7 (“Strongly agree”) for six statements about how much the characteristic features of the music would motivate a person during exercise. The range of total scores is 6–42, with scores below 24 indicating low motivational quality or an oudeterous (neutral) nature, those in the middle range (24–35) representing moderate motivation, and scores over 35 denoting highly motivating material [28].

The members of the video group (*n* = 4, mean age 41 years, SD 16.2 years) first watched the DVD and assessed all three songs separately, using the BMRI-2. Then they listened to the music only (without video) and rated the motivational quality of each song. The music group (*n* = 4, mean age 42.8 years, SD 15.8 years) assessed the motivational qualities of the songs first, then watched the DVD and appraised the music and video content together. In addition, both groups moved to the DVD and rated the motivational qualities of the music during movement. Music and video together received higher motivation ratings than did the music alone, from both groups (see Table 2).

### The movement program

The exercises in the videos are based on PA recommendations [5] and include exercises to improve or maintain aerobic fitness, muscle strength, balance, and coordination (including motor and rhythm coordination) [31]. All three songs begin with the Mud Mates getting up from a sofa. Each song has its own movements, which are performed to the beat of the music. The videos serve to encourage and motivate mother and child to exercise together and allow them to choose suitable movements for themselves from one to three variations.

The first song, “Mutaveijarit”, is accompanied by movements to improve aerobic fitness (walking, jumping, stepping, and shaking one’s whole body), postural balance (standing on one leg), and motor coordination (pelvic and midriff control, and agility). The second song, “Karibialainen kala”, involves movements to improve dynamic balance (moving the center of gravity to the edge of the area of support) and motor coordination (Caribbean dance movements such as swaying from side to side and making stepping motions). The third song, “Kuravelli”, entails movements to improve muscle strength (squats and lunges) and aerobic fitness (walking, jumping, and the side gallop). The last song, “Mutaveijarit”, (the same as the first) combines movement elements from all three previous songs.

### Data collection

The baseline data collection (with body-weight and questionnaire-based measurement) will take place during the personal contact of sampling for the NELLI study. Information on the accelerometer-based measurements will be supplied to participants at the same time. The timing of the data collection related to these measurements, the exercise diaries, and the questionnaires is described in detail in Table 3.

**Table 3 Tab3:** Moving Sound data collection and measurements at baseline and the 1st, 2nd, and 8th week after baseline measurement

Data collection	Baseline	1st week	2nd week	8th week
Measurements and exercise diaries				
Accelerometer measurements		X	X	X
Exercise diaries		X	X	X
Weight	X			
Questionnaires				
Background questions	X			
Weight		X	X^a^	X
Earlier physical activity (LTPA)	X			
Current physical activity and sitting time	X		X^a^	X
Motivation to exercise (EIS and TPB)	X		X^a^	X
Quality of life (15 D)	X			
Depression (BDI)	X			
Anxiety (SAI)	X			
Work ability	X			
Perceived health	X			
Mother's musical background			X^a^	
Motivational quality of the music			X^a^	
Other motivation-related factors			X^a^	X^a^
Experiences of use of the video			X^a^	X^a^
Perceived changes in PA			X^a^	X^a^

^a^Intervention group

### The measurements and exercise diaries

Objective measurement of the SB and PA of the mothers and children will be conducted in the first, second and eighth weeks of the intervention via accelerometer use during waking hours. The mothers’ body weight will be measured at baseline.

Participants will be instructed to complete exercise diaries for the time for which they wear the accelerometers. The mothers will be asked to indicate their working hours and actual exercise, such as walking, jogging, running, swimming, biking, gym workouts, and dancing in the diaries. Start and end time of the exercise are to be filled in. Also, the participants will be instructed to assess the perceived exertion their exercise involves numerically: 1 = light PA, with no shortness of breath or sweating at all; 2 = moderate PA, with some shortness of breath or sweating; and 3 = vigorous PA, indicating heavy breathing or increased sweating. If more than one type of exercise is performed in the course of a day, the participants are to include all of these in the diaries. Mothers are asked to record the child’s exercise time at daycare or school and at home, and the time spent in PA, in the children’s diaries.

### Questionnaires

Information on participants’ background, PA, screen time, motivation to exercise, and self-reported height and weight, along with information on quality of life, will be collected at the baseline by means of the same questionnaires used for the NELLI five-year follow-up study (based on original and one-year follow-up questionnaires for the NELLI cohort). At two weeks after baseline, information on PA, screen time, self-reported weight, musical background, and motivation to exercise by means of a movement-to-music video program will be collected for the intervention group. At the eighth week after baseline, information on PA, screen time, motivation to exercise, and (self-reported) weight will be collected from all participants. Information on motivation to exercise by using the movement-to-music video program will be collected from the intervention group. Information on the children’s PA and screen time will be collected at baseline and the second and eighth week after baseline via questionnaires.

The information on participants’ background includes data on socioeconomic status, smoking, and height and weight. The participants of the intervention group will be asked for information on the mother’s musical background.

Mothers’ earlier PA will be examined at baseline via a leisure-time physical activity (LTPA) questionnaire, addressing the amount, duration, and intensity of PA within a typical week over the previous year. The validity and reliability of these questions have been examined previously [32]. The questionnaire on participants’ current PA and time spent in a sitting position in various contexts (on both weekdays and weekends) is the same as that utilized in the national Health 2011 Survey [33] and FINRISKI 2011 Study [34] in Finland, intended to ascertain how fully people meet the PA recommendations and how much they tend to sit. The questionnaire on the child’s typical exercise and screen time is based on the same questionnaire used in the Finnish project on health monitoring among children and young people (LATE) [35], with a protocol reported upon earlier [36]. There are separate questions on outside activities, exercises, and screen time. Both weekdays and weekends are covered. Responses to questionnaire items on current PA and on time spent in a sitting position and screen time will be examined at baseline and after week 8 for all participants, as will the figures for just after the second week for the intervention group.

The instrument examining motivation to exercise is based on the Finnish version [37] of the Enjoyment in Sport (EIS) questionnaire [38] and also addresses some factors motivating exercise [39]. Investigators involved in the present study modified the questions to be appropriate for exercising with children, for example, the statement “I like exercising” was changed to “I like exercising with a child.” Motivation and intention to encourage the child to perform PA will be examined by means of a short version of a theory of planned behavior (TPB) questionnaire [40]. In the first phase, this questionnaire was developed on the basis of the TPB manual instructions at University of Jyväskylä, Finland. In the second phase, it was pre-tested for clarity of language and suitability for the local culture by five experts in various relevant fields (physical education, exercise physiology, kinesiology, and health science). In the third phase, items with low reliability indices were excluded on the basis of pilot data collection from around 100 parents of 4–7-year-old children [41]. The final version of the TPB short form used in the present study is composed of elements on behavior, intention, attitudes to the behavior, and perceived control over the behavior. Motivation questions will be evaluated at baseline and after the eighth week for all participants and, in addition, for the intervention group after week 2.

The relationship between SB or PA and quality of life, depression, and anxiety is also of interest. Assessments of quality of life, depression, anxiety, and work ability will be performed via Finnish versions of the validated indicator. Quality of life will be assessed via the 15D instrument [42], depression via Beck’s Depression Inventory (BDI) [43], and anxiety by means of the State Anxiety Inventory (SAI) [44]. A visual analogue scale (VAS) will be used in the assessment of perceived health and an 11-point Likert scale for work ability. The 15D has 15 separate items: ability to be physically active, vision, hearing, breathing, sleeping, eating, communicating, elimination, normal functions, mental health, signs and symptoms, depression, anxiety, vitality, and sexuality. The BDI, in turn, is based on 21 distinct items for measuring the severity of depression in terms of a list of four statements. The SAI, a sub-scale of the State-Trait Anxiety Inventory (STAI), has 20 items for assessing “how I feel right now” on a four-point scale (“not at all” – “somewhat” – “moderately so” – “very much so”). Ten of the 20 statements typify presence and the other 10 absence of anxiety. Perceived health is an important factor when one wishes to predict functional capacity and health [45], and it will be measured via a VAS. Perceived work ability at the moment, relative to lifetime best, will be evaluated on an 11-point Likert scale, where 0 = total disability and, 10 = work ability at its best ever. Perceived deficiency of work ability in midlife is associated with accelerated weakening in health and functioning in later life [46]. Quality of life, depression, anxiety, perceived health, and work ability assessment will be evaluated for all participants at baseline.

In addition, there is a questionnaire for subgroup analysis, made up of questions for the intervention group. The items on mother’s musical background include questions about prior singing, playing of an instrument, dancing, and listening to music. The questionnaire on the motivational quality of the music is based on the BMRI-2. In this, the music will be rated on a scale of 1 (for strong disagreement) to 7 (for strong agreement) with each of six statements about how much the characteristic features of the music would motivate a person during exercise [29]. Experiences of use of the movement-to-music video program, factors (other than music) motivating exercise, and perceived changes in PA will be assessed via a questionnaire that was developed by investigators working on the present study. Participants will rate their experiences of use of the video on a scale of 1 (“Hard”) to 3 (“Easy”). Factors motivating exercise (the video’s characters, movements, and ambience and exercising with the child) will be rated on a scale of 1 (for “Strongly disagree”) to 7 (for “Strongly agree”). Perceived changes in PA will be rated between 1 (“Much less than earlier”) and 5 (“Much more than earlier”). In addition, participants will be asked about their actual activity while watching the video, including how well they performed the exercises in accordance with the video instructions, and about perceived personal shortcomings in physical fitness during completion of the video exercises. The questionnaires for subgroups were pre-tested by a group of eight physiotherapists and piloted in a separate pilot study. Items on mother’s musical background and BMRI-2 scores will be evaluated after second week, other questions after weeks 2 and 8.

### Statistical methods

The effects of the intervention will be analyzed in line with the intention-to-treat principle through comparison of the changes in the main outcomes between intervention and control group participants. Level of PA, sedentary time, and body weight will be compared between the intervention and control group. All differences in the afore-mentioned outcomes between groups will be examined via linear regression. If the assumptions of linear regression are violated, ordinal or logistic regression analysis will be used. Non-parametric methods (specifically, the Mann-Whitney *U*-test) will also be used to describe differences between groups if needed. Subgroup analysis within the intervention group will be conducted with the mother’s motivation to exercise with the movement-to-music video program and her musical background as covariates. The intervention group will be split into two classes on the basis of these (dummy) variables. These variables will be used to explain differences in exercise activity between mothers in the intervention group. A significance level of 0.05 will be used for all analysis.

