**Fig. 1 Fig1:**
[figure not shown]
Flow chart, estimates for sample size, and randomization for the study

For the randomization, there was not an appointment order list and the total number of participants was unknown. Randomization was performed for blocks of four participants, in a 2:2 ratio: two mother-child pairs in the intervention group for two pairs of control participants. In practical terms, four random numbers were generated, and the pairs associated with the two largest were assigned to the experimental group and the two lowest to the control group. For allocation of participants, an appointment order list for the NELLI five-year follow-up study is being used. Mothers are randomized to the intervention or control group by means of sealed envelopes in the contact for sampling for the NELLI study.

The recruitment started in November 2014 and will continue until December 2015. Because season-to-season changes in Finland are large (with cold and snowy winters, rain in the spring and fall, and a warm summer), seasonal differences in PA levels may present themselves [26, 27]. Though the intervention takes place in the home, we have paid attention to this effect by performing the intervention throughout the year.

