### Power calculations

On the basis of the Moving Sound pilot study, it is assumed that the mean sedentary (i.e., sitting or lying down) time will be 7 h 40 min per day at baseline. It is also assumed that the reduction in sedentary time in the intervention group at the end of the study will be around 6 % while the control group’s figure remains unchanged. Differences of groupwise means are tested via T-tests. Power calculations for the study (see Table 1) show that if the significance level is 0.05 (α = 0.05) and the power of the study is to be 80 % (β = 0.80), effect size varies from 0.357 to 0.500 and approximately 63–124 mother-child pairs per group are needed.

**Table 1 Tab1:** Power calculations for the primary outcome of the study

Primary aim: decrease participants’ sedentariness by using movement-to-music video material							
Sedentary time (mean 7 h 40 min, α = 0.05)			Intervention: Accelerometer and DVD group		Control: Accelerometer group		Number of participants (mother + child pair) needed per group
Reduction of sedentary time	power	effect size	Mean	SD	Mean	SD	
5.4 %	β = 0.80	0.357	435 min	70 min	460 min	70 min	124
5.4 %	β = 0.80	0.385	435 min	65 min	460 min	65 min	107
5.4 %	β = 0.80	0.417	435 min	60 min	460 min	60 min	91
6.5 %	β = 0.80	0.429	430 min	70 min	460 min	70 min	86
6.5 %	β = 0.80	0.462	430 min	65 min	460 min	65 min	74
6.5 %	β = 0.80	0.500	430 min	60 min	460 min	60 min	63

α = significance level, β = power of the test

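### The stated fallback to ordinal or logistic regression lets the data choose the effect measure, and the main comparison of changes names no baseline covariate and does not match the t-test on which the trial was sized

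*Protocol article*

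**What the plan says.** The Statistical methods section of the protocol article describes an intention-to-treat analysis "through comparison of the changes in the main outcomes between intervention and control group participants". Linear regression is the default model for these group differences. The only covariates named anywhere in that section belong to the subgroup analysis inside the intervention group.

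The same section sets the fallback: "If the assumptions of linear regression are violated, ordinal or logistic regression analysis will be used". Mann-Whitney is added as a descriptive supplement where needed. The section does not say what counts as a violation, where minutes would be cut into categories, or when ordinal rather than logistic regression applies.

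Power calculations describes a different test: "Differences of groupwise means are tested via T-tests". It takes from the pilot that "the mean sedentary (i.e., sitting or lying down) time will be 7 h 40 min per day at baseline". Table 1 compares means of 435 or 430 min with 460 min, with SDs of 60, 65 or 70 min in each group, and gives 63 to 124 pairs per group.

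A pre-intervention accelerometer value exists for both groups. The interventions section and Table 3 place accelerometry in weeks 1, 2 and 8, and the intervention group gets the DVD only at the end of week 1.

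**The concern.** Sedentary time and activity time are continuous, measured in minutes or as a share of wear time. Ordinal or logistic regression of such data generally means grouping them. That discards information and changes the quantity estimated, from minutes per day to an odds ratio. Because the switch depends on an undefined check made on the trial data, the result could be reported on either scale, and a reader could not tell whether the choice was independent of the findings. Skewed or heteroscedastic residuals do not require the switch: the mean difference can be kept and only its standard error handled differently.

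The second issue is the fit between planning and analysis. A change from week 1 to week 8 does not have the same variance as a single week's value. The two are linked by the within-person correlation, which the article does not give. The tabulated power therefore carries over to a comparison of changes only under a condition that is not stated. Naming the week-1 value as a covariate would largely remove the dependence and would also correct for chance baseline imbalance.

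**Working it through.** **Inputs.** From Power calculations and Table 1: alpha 0.05 (two-sided reproduces the table), power 80 %, difference 25 or 30 min, SD 60 to 70 min, equal groups. Not in the article, so assumed: correlation r between the week-1 and week-8 values, from 0.3 to 0.8, with equal SD at both times.

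**Step 1. Reproduce Table 1.** n per group = 2 × (1.960 + 0.842)² × (SD/difference)² = 2 × 7.849 × (SD/difference)².
- 25 min, SD 70: 15.70 × 7.84 = 123.1, rounded up to 124.
- 30 min, SD 60: 15.70 × 4.00 = 62.8, rounded up to 63.
- The other four rows give 107, 91, 86 and 74.

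All six match, so the arithmetic of the table is right for a t-test of group means.

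**Step 2. Carry the table over to the planned analysis.** Read the Table 1 SD as that of a single-time value.
- Unadjusted change: SD × √(2(1−r)). This equals the tabulated SD at r = 0.5 and exceeds it below 0.5.
- Linear model adjusted for week 1: SD × √(1−r²).
- Variance ratio, adjusted to change: (1−r²)/(2(1−r)) = (1+r)/2.

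Power at 124 per group, 25 min, SD 70 (normal approximation, as in step 1; the exact t-test differs by less than half a percentage point):

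| r | SD of change | SD adjusted | Power, change | Power, adjusted | n for 80 %, change | n for 80 %, adjusted |
|---|---|---|---|---|---|---|
| 0.3 | 82.8 | 66.8 | 66 % | 84 % | 173 | 112 |
| 0.4 | 76.7 | 64.2 | 73 % | 87 % | 148 | 104 |
| 0.5 | 70.0 | 60.6 | 80 % | 90 % | 124 | 93 |
| 0.6 | 62.6 | 56.0 | 88 % | 94 % | 99 | 79 |
| 0.7 | 54.2 | 50.0 | 95 % | 98 % | 74 | 63 |
| 0.8 | 44.3 | 42.0 | 99 % | nearly 100 % | 50 | 45 |

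For equal power, the unadjusted change needs 2/(1+r) times as many pairs as the adjusted model: 1.54 times at r = 0.3 and 1.11 times at r = 0.8.

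**Step 3. Cost of the fallback.** The article fixes no categories, so two ends are shown for a normal outcome with the Table 1 inputs (25 min, SD 70).
- Median split with logistic regression: the proportions on the two sides of the cut are Φ(0.357/2) = 0.571 and 0.429, an odds ratio of about 1.77. Efficiency is about 2/π = 0.64, so 124 pairs act like 124 × 0.64 ≈ 79. Power is about 61 %, and 195 pairs per group would be needed for 80 %.
- Ordinal model with many categories: efficiency is close to that of a rank test, 3/π = 0.955, so 124 pairs act like about 118. Power is about 78 %.

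The loss of information thus ranges from small to large with the unstated grouping. The move from minutes to an odds ratio occurs in both.

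**The case against.** The strongest reply is that linear regression is the default and can carry a baseline term. An article may leave its covariate list to the full analysis plan, and regressing the change on group plus baseline gives the same group effect as regressing the week-8 value on group plus baseline. This stands. A reader might infer that the baseline value is excluded from the model, but the article does not say so; it only names no such covariate.

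A reader might also infer that the trial is underpowered. The article does not support that as a general statement. Table 1 reproduces exactly. If its SD is already the SD of change, 80 % holds as stated. If it is a single-time SD, 80 % still holds for r of 0.5 or more. Expected recruitment of 251 to 335 pairs is about 125 to 167 per group before losses. At 125 per group with 30 min and SD 65, an unadjusted change has 87 % power even at r = 0.3. With the least favourable row (25 min, SD 70) and 167 per group, it has 79 % at r = 0.3 and 84 % at r = 0.4. The shortfall needs low r together with an unfavourable row or recruitment.

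The 61 % figure depends on a median split that the article does not mention, and Mann-Whitney is there only to describe. Both points are fair. Nor does the remark that "seasonal differences in PA levels may present themselves" make a season covariate necessary: recruitment is spread over the year, and blocks of four along an appointment list tend to balance season.

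None of this answers the fallback sentence. It commits to a change of model, so it is a stated rule and not a detail left for later.

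**Conclusion.** The point holds in two parts.

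The firmer part is the fallback. The article commits to replacing a mean difference in minutes with an odds ratio after the data are seen, without a trigger or cut-point. That rests on the text alone. Its cost in power at 124 per group runs from about 2 percentage points (fine ordinal model) to about 19 (median split), depending on a grouping that is not stated.

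The conditional part is the mismatch between a t-test of group means and a comparison of changes, with no baseline covariate named. Its size rests on reading the Table 1 SD as a single-time SD, on equal SDs at both weeks, and on r. For 25 min, SD 70 and 124 per group, naming the week-1 value gains about 18 points at r = 0.3, about 10 at r = 0.5, and almost nothing at r = 0.8. It is a free improvement, not the correction of a wrong sample size.

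The change should be made, but nothing here shows the trial to be unsound.

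**What to change.** 1. In Statistical methods, state the primary model as linear regression of the week-8 accelerometer value (or the change) on group, adjusted for the week-1 value of the same outcome.
2. Replace the fallback sentence: if residual assumptions fail, keep the same mean difference and report robust (HC3) or bootstrap confidence intervals.
3. Move ordinal, logistic and Mann-Whitney analyses of the accelerometer outcomes to sensitivity analyses.
4. In Power calculations, describe the test that matches this model, and say whether the Table 1 SD is that of a single week or of the change. If a correlation is assumed, state it.

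The cost is a few sentences. No new data are needed, since week-1 accelerometry is already collected in both groups before the DVD is given, and the tabulated sample size can stay.

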**Fig. 2 Fig2:**
[figure not shown]
Intervention for eight weeks

In addition, the intervention (i.e., movement-to-music) group will receive the DVD and YouTube-link to videos by e-mail or cell phone, in line with their choice between these, at the end of the first week. The DVD is the preferred option, because of the larger image and better sound when it is played through a television set. The YouTube-link is intended as an alternative to be used, for example, during trips or if the DVD breaks. Mothers in the movement-to-music group will be instructed to watch the program on the DVD or on the Internet every other day with their 4–7-year-old child. The mothers and children will be instructed to move to the video and report their exercise in the structured diaries. Mothers will also use the Brunel Music Rating Inventory-2 (BMRI-2) to assess the motivational quality of the music used in the movement-to-music video [28, 29].

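### Motivation with the video is rated after delivery, split into two classes and used to explain activity within the intervention group, with no stated adjustment for pre-programme activity

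*Protocol article*

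**What the plan says.** Statistical methods in the protocol article sets the population ("Subgroup analysis within the intervention group will be conducted"), names the two variables (the mother's motivation to exercise with the video programme, and her musical background), sets their form ("The intervention group will be split into two classes on the basis of these (dummy) variables") and gives the purpose: "These variables will be used to explain differences in exercise activity between mothers in the intervention group". The 0.05 level is applied to every analysis, and this one is not marked as exploratory.

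The timing is given elsewhere. Under The interventions, the DVD and link reach the intervention group "in line with their choice between these, at the end of the first week". Under Questionnaires, two weeks after baseline, "musical background, and motivation to exercise by means of a movement-to-music video program will be collected for the intervention group"; motivation with the video is asked of this group again at week 8. The paragraph on the intervention-group questionnaire adds: "Items on mother’s musical background and BMRI-2 scores will be evaluated after second week, other questions after weeks 2 and 8". It describes the musical items as covering earlier singing, playing, dancing and listening.

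A different, general measure of motivation (EIS and TPB) is available in both arms before the programme: "Motivation questions will be evaluated at baseline and after the eighth week for all participants". Table 3 also places accelerometer measurement in week 1, before delivery, in both groups.

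**The concern.** Explaining activity by motivation treats motivation as coming first. Here it is rated only once the mother has had the video for about a week. A mother who has exercised with it and enjoyed it may rate it higher for that reason, so the predictor may be partly a product of the outcome.

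The second problem applies to both variables. Mothers who are generally active may rate an exercise video as more motivating, and may also have more of the musical history asked about, which includes dancing. They would be more active in week 8 with or without the video. The analysis has no controls to show this and no stated adjustment for activity before the programme.

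Third, splitting a score into two classes discards information in a group that is already only half of the trial. At stake is a secondary conclusion: a significant class difference could be reported as showing why some mothers exercised more, when the design cannot separate that from the other explanations.

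**Working it through.** **Order of events.**
- Week 1: accelerometer in both groups, no video.
- End of week 1: video delivered to the intervention group.
- Week 2: accelerometer; after it, the first rating of motivation with the video, and the musical-background items.
- Week 8: accelerometer; video-motivation items again.

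Every rating of motivation with the video therefore follows at least a week of access. Week-1 activity is the only accelerometer measure that precedes the programme. The musical items are asked late but refer to the past.

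**Arm sizes.** The plan gives no figure for this analysis, so I take arm sizes from Power calculations. Table 1 reproduces with n = 2(1.960 + 0.842)² (SD/difference)². For 25 min and SD 70 this is 15.70 × 7.84 = 123.1, so 124; for 30 min and SD 60 it is 15.70 × 4 = 62.8, so 63. The other four rows (107, 91, 86, 74) also agree. Expected recruitment of 251–335 pairs gives about 125–167 per group.

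**Reverse causation (illustration; the correlations are assumed).** Suppose motivation only reflects exercise already done, with correlation ρ, and has no effect on it. After a median split the expected class difference in exercise is 2 × √(2/π) × ρ = 1.596ρ SD: 0.32 SD at ρ = 0.2 and 0.80 SD at ρ = 0.5. Share of 4,000 simulated trials with p < 0.05:

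| ρ | 63 mothers | 124 mothers |
|---|---|---|
| 0.2 | 24 % | 42 % |
| 0.3 | 48 % | 77 % |
| 0.5 | 92 % | 99.8 % |

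These are not estimates for this trial. They show that the planned test can often be significant when causation runs entirely the other way.

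**Information lost by two classes (assumes a roughly normal score; no cut-point is stated).** The share kept when a fraction p lies above the cut is φ(z)²/[p(1 − p)], where φ is the normal density and z the cut-point.
- Median cut: 0.3989²/0.25 = 0.637, a loss of about 36 %; 125 mothers carry the information of 125 × 0.637 ≈ 80.
- 25/75 cut: 0.3178²/0.1875 = 0.539, a loss of about 46 %.

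**Detectable class difference at 80 % power, two-sided 0.05.** Even split: 0.72 SD with 63 mothers, 0.51 SD with 124. A 25/75 split: 0.83 and 0.59 SD.

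**Power of an interaction with a continuous baseline score.** With the score in SD units, the difference in slopes between arms has variance 2σ²/n, as for the main effect. A change in effect per SD half the size of the planned effect therefore needs four times the Table 1 numbers, about 4 × 63 = 252 to 4 × 124 = 496 per group, against an expected 125–167.

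**The case against.** The strongest reply is that the plan asks for nothing more than a description within one arm. Its stated purpose concerns differences between intervention mothers; neither the aims nor Statistical methods promises to show for whom the intervention works, and no interaction is specified. That stands. A reader might infer from the subgroup label that effect modification is claimed and that the analysis fails at it. The text does not support that reading, and the point does not rest on it.

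Controls have no video, so motivation with it can be studied only within the intervention group. That stands too. Baseline EIS/TPB motivation answers a different question and does not replace it. If exercise activity here means use of the video, controls have none and a between-group interaction on that outcome has no meaning.

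A reader might extend reverse causation to both variables because both are collected after delivery. The musical items concern earlier history, which a week with a video cannot create; late collection adds at most recall error or missing answers. Confounding by general activity still applies to them.

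A reader might also take the 36 % loss as a property of the plan. It is conditional: the cut-point is not given and may be left to the analysis plan, and some musical items may be categorical by nature.

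What remains is that the two-class form, the explanatory aim and the timing of the motivation rating are fixed in the text. No adjustment for earlier activity is stated to offset them.

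**Conclusion.** The point holds as a limited correction to a secondary analysis. As described, a class difference in activity cannot be read as motivation or musical background explaining activity. For motivation with the video, the rating may follow from exercise done; for both variables, the difference may only reflect mothers who were more active beforehand. How large either distortion would be cannot be derived from the documents. The simulated 24–92 % (63 mothers) and 42–99.8 % (124 mothers) rest on assumed correlations of 0.2–0.5 and a median split. The loss from dichotomising is about 36 % at best for a roughly normal score, and more for uneven cuts. The intention-to-treat comparison and the sample size are unaffected.

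**What to change.** Reword Statistical methods as follows.
- Where a variable is a score, enter it as continuous in the within-arm regression; keep categories only for items that are categorical by nature.
- Adjust for week-1 accelerometer activity.
- Relate week-2 motivation with the video to week-8 activity, so that the rating precedes the outcome. This reduces reverse causation without removing it, because early use may drive both.
- Report the result as an exploratory association within the intervention group, not as an explanation of response.

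If the trial wants to know whether motivation modifies the effect of the intervention, add one exploratory term, group by baseline EIS/TPB motivation (continuous), to the between-group regression of accelerometer outcomes.

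None of this needs new data. The cost is wording, one covariate and, optionally, one interaction term with low power, so a null interaction should not be read as evidence of a uniform effect. The same test for musical background is not available from the planned data, since only the intervention group is asked. Adding the items for controls at week 8 would mean new collection at a different time from the intervention group, with recruitment already under way.
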